#### 2.4.7. Statistical Analysis

Data analysis will be performed using the Statistical Package for the Social Sciences version 24 (SPSS v24). A fully licensed version of SPSS is available through the university tp which the corresponding author of this manuscript belongs.

Descriptive statistics will be used to summarize the sample characteristics. Qualitative variables will be presented as percentages (%), while quantitative variables will be reported as mean ± standard deviation or as median and interquartile ranges (IQR).

The statistical distribution of the data will initially be assessed using the Shapiro–Wilk test. To ensure baseline balance, demographic characteristics and initial assessments will be compared between groups using independent samples *t*-tests for normally distributed data, the Mann–Whitney U test for non-normally distributed variables, and Chi-square tests for categorical data.

The primary analysis of the intervention’s effect will be conducted using a two-way mixed-design ANOVA, with ‘Group’ (Experimental vs. Control) as the between-subjects factor and ‘Time’ (Pre- vs. Post-intervention) as the within-subjects factor. The Group × Time interaction will be the primary effect of interest to determine efficacy. In the event of significant interactions, post hoc pairwise comparisons with Bonferroni correction will be performed.

Two-sided 95% confidence intervals will be calculated, and statistical significance will be set at *p* ≤ 0.05. No subgroup or exploratory analyses are planned for this study to maintain adequate statistical power.

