#### 2.4.6. Sample Size Calculation

The sample size has been calculated using the software G*Power 3.1.9.7 (3.1.9.7v; Statistical Power Analyses for Windows, Universität Düsseldorf, Germany). The calculation was based on the COMP tool. According to a previous study [39], assuming an effect size of 0.7 for the COMP tool, an alpha value (α) of 0.05, a power (1 − β) of 0.80, and a 1:1 randomization ratio, a total of 52 patients will be needed. Assuming a 10% dropout rate, a total of 58 participants should be included in this study (29 participants in the experimental group and 29 participants in the control group).

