## 3. Results

The results will be published as a peer-reviewed article. We will summarize the results in three tables. The first table will outline the descriptive characteristics of the sample. The second table will compare the primary outcomes between groups at baseline. The third table will present post-intervention outcomes, detailing both intra-group and between-group changes, with effect sizes calculated using Cohen’s d. Additionally, the article will include a figure illustrating the flow diagram.

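### Baseline significance tests cannot ensure balance and feed nothing; pre-specified adjustment for baseline COPM and EDSS would do what they are meant to do

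*Protocol article*

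**What the plan says.** The Statistical Analysis section (2.4.7) of the protocol article introduces the baseline comparison with its purpose: "To ensure baseline balance, demographic characteristics and initial assessments will be compared between groups using independent samples" t-tests where data are normal, Mann–Whitney tests where they are not, and Chi-square tests for categorical variables. The section's general threshold is "statistical significance will be set at *p* ≤ 0.05", and "Two-sided 95% confidence intervals will be calculated". The Results section adds a table for this: "The second table will compare the primary outcomes between groups at baseline".

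The efficacy analysis in 2.4.7 is a mixed ANOVA with Group and Time (pre, post), and the Group × Time interaction is the effect of interest. No covariate is named. EDSS and type of MS are collected under Descriptive Measures (2.4.4). Allocation (2.4.1) is by a random number list, with no stratification described. The planned size is "29 participants in the experimental group and 29 participants in the control group".

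**The concern.** The article gives the baseline tests a task that they cannot perform. A significance test describes the data after allocation and cannot bring about balance. In a randomised trial it also tests a hypothesis already known to be true, so p ≤ 0.05 is a chance event and p > 0.05 is no evidence that the arms are alike.

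An imbalance matters according to its observed size and how strongly the variable predicts outcome, not its p-value. The tool that deals with this is adjustment fixed in advance, and the stated efficacy model has none. At stake are the precision of the primary comparison and its protection when chance produces an imbalance. There is also the risk that a column of baseline p-values is read as showing comparability, or is used to choose adjustments after the fact.

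**Working it through.** **Inputs from the documents.** 58 participants, 29 per arm; before dropout, "a total of 52 patients will be needed" (26 per arm); "assuming an effect size of 0.7 for the COMP tool"; significance at 0.05; two time points. **Assumed, not in the documents:** baseline tests are two-sided, as the confidence intervals are; pre–post correlation r from 0.3 to 0.8; equal variances before and after; baseline imbalances D chosen for illustration.

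**1. The plan's own figure.** For effect size 0.7 and power 0.80, a t-test at one-sided 0.05 needs 26 per arm (power 0.801), which is 52, and 52 / 0.90 = 57.8, rounded up to 58. A two-sided test would need 34 per arm. That is a separate matter; 29 per arm is taken as given here.

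**2. What the baseline test lets through.** The largest non-significant observed difference is t(0.975; 2n − 2) × √(2/n).
- 29 per arm: 2.003 × 0.2626 = 0.526 SD.
- 26 per arm: 0.557 SD.
- An observed 0.5 SD at 29 per arm gives p = 0.062, so it always passes.
- On any one variable, chance alone gives an observed difference of at least 0.5 SD in about 6% of trials, and one between 0.3 and 0.526 SD in about 21%.

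**3. What it flags.** Counting age, sex, MS type, EDSS, symptoMScreen, two COPM scores, MFIS, FSS, arm curl, grip, pinch, finger tapping, 9HPT, Purdue and coin rotation gives 16 variables (my count). If they were independent, P(at least one p ≤ 0.05) = 1 − 0.95^16 = 0.56. Correlation between them lowers this.

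**4. What the efficacy model does with the outcome's own baseline.** With two time points, Group × Time is a two-sample comparison of change. If the arms differ by D at baseline, the expected post-intervention difference without a treatment effect is r × D. The change contrast is then rD − D = −(1 − r)D. Its size for D = 0.5 SD:

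| r | (1 − r) × 0.5 |
|---|---|
| 0.3 | 0.35 SD |
| 0.5 | 0.25 SD |
| 0.7 | 0.15 SD |
| 0.8 | 0.10 SD |

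The direction is opposite to the baseline difference (regression to the mean). ANCOVA on baseline removes this term.

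**5. Precision.** In units of the outcome variance, the change score has variance 2(1 − r) and ANCOVA has residual variance 1 − r². The ratio is (1 + r)/2: 0.65, 0.75, 0.85 and 0.90 for r = 0.3, 0.5, 0.7 and 0.8. ANCOVA therefore removes 10% to 35% of the variance over this range, before the small cost in degrees of freedom.

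**6. A covariate outside the model.** Suppose EDSS correlates 0.3 or 0.5 with COPM change (assumed), with no treatment effect and 29 per arm. In 200,000 simulated trials for each correlation:
- Rejection over all trials: 5.0% and 5.0%.
- Among trials whose EDSS test is non-significant: 4.8% and 4.3%.
- Among trials with an EDSS imbalance of 0.40 to 0.52 SD, about 8% of all trials: 6.7% and 10.3%, with a mean shift in change of 0.13 and 0.23 SD.

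**The case against.** The strongest reply is that the unadjusted randomised comparison is already valid. This stands: step 6 shows the overall error rate at 5%, and below 5% among trials that pass the baseline test. A reader might infer that the screen inflates false positives to roughly 7% to 10%. That figure applies only under an assumed correlation of 0.3 to 0.5 and in the roughly 8% of trials with an imbalance of 0.40 to 0.52 SD.

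Three other stronger readings are tempting and do not hold:
- *The efficacy analysis ignores baseline imbalance.* For the outcome's own baseline this is wrong, because Group × Time subtracts it. It holds for EDSS, MS type and demographics only.
- *The tests miss a 0.5-SD difference more than half the time.* The arithmetic is right (53.5% at 29 per arm), but it supposes a true population difference, which randomisation rules out. The observed threshold in step 2 is the relevant figure.
- *The plan declares the arms balanced when p > 0.05.* The stated purpose points that way, but the article writes no such rule, and no action if p ≤ 0.05. The baseline table in the Results section does not mention p-values.

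It may also be said that covariates can be left to a statistical analysis plan that is not shown, and that no figure in the article shows EDSS to predict COPM change. Both are fair. But the article does not leave the primary model open: it names a two-factor ANOVA and the interaction as the test of efficacy. The case for baseline COPM does not depend on EDSS.

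**Conclusion.** The point holds in a limited form. The stated purpose of the baseline tests is wrong: they cannot ensure balance, they pass any observed difference below about 0.53 SD at 29 per arm, and nothing in the plan uses their result. The efficacy model handles the outcome's baseline by subtraction, which leaves (1 − r) × D of a chance difference in the contrast, and it leaves out a plausible prognostic variable that is already collected.

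Validity is not in question, as the overall type I error remains 5%. What is lost is precision (10% to 35% of the variance for r from 0.8 to 0.3) and protection in a trial that happens to be imbalanced. These sizes rest on equal variances and on correlations that the article does not give. Removing the tests alone would be a reporting correction; pre-specified adjustment improves the primary analysis itself at almost no cost.

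**What to change.** In 2.4.7:
- Delete the clause that gives baseline balance as a purpose, together with the baseline t, Mann–Whitney and Chi-square tests. Present baseline data by arm descriptively, without p-values, and word the baseline table in the Results section to match.
- Pre-specify the efficacy comparison as ANCOVA of the post-intervention score on group, with the baseline value of that outcome and EDSS as covariates, whatever the baseline table shows.
- If the mixed ANOVA is kept, add EDSS and EDSS × Time. An EDSS main effect alone would leave the Group × Time contrast unchanged. This option still does not adjust fully for the outcome's own baseline.
- State that baseline comparisons will not be used to claim comparability or to choose covariates.

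The cost is one or two degrees of freedom (two covariates take the residual from 56 to 54 with all 58 analysed) and the loss of a customary p-value column. No extra participants, visits or measurements are needed.

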#### 2.4.4. Descriptive Measures

An independent researcher, blinded to the patients’ group allocation, will collect all data at baseline and after the intervention. To characterize the clinical profile of the participants included in the study, the Expanded Disability Status Scale (EDSS) [22] and the ‘symptoMScreen’ [23] will be used. The EDSS is a widely used method for quantifying disability in individuals with multiple sclerosis. It ranges from 0 (normal neurological function) to 10 (death due to MS), based on neurological examination and the assessment of ambulation and functional systems. The ‘symptoMScreen’ tool consists of 12 domains, each rated on a 7-point Likert scale ranging from 0 (not affected at all) to 6 (total limitation/unable to perform most daily activities). In addition, sociodemographic and anthropometric characteristics will also be collected, including age, sex, and type of MS.

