#### 2.4.5. Outcome Measures

The primary outcome in this study will be the Canadian Occupational Performance Measure (COPM) [17]. This tool measures the perception of problems related to the overall quality of performance, development and satisfaction with particular occupations. This is a standardized instrument that was previously validated [17,24] and used [25] in MS patients. The COPM will be used under a formal license that will be obtained through official channels to ensure full compliance with copyright and intellectual property regulations.

The secondary outcomes include fatigue level, upper limb strength, motor speed and manual dexterity. The level of fatigue will be assessed with the Modified Impact Fatigue Scale (MFIS) [26] and the Fatigue Severity Scale (FSS) [27]. The MFIS consists of items from which a total score is obtained and for each subscale. Scores range from 0 to 36, with higher scores indicating a greater impact of fatigue on activities. The FSS consists of nine items that are rated on a scale of 1 to 7. A higher score indicates a higher agreement with the statement presented in each item. This scale is recommended for use in clinical practice and research in MS patients [26,28].

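### The primary Group × Time ANOVA is a change-score t-test; adjusting post-intervention COPM for baseline would usually be more precise and would correct chance baseline imbalance

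*Protocol article*

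**What the plan says.** Section 2.4.7 (Statistical Analysis) states that the primary analysis "will be conducted using a two-way mixed-design ANOVA". Group is the between-subjects factor and time, with a pre and a post level, is the within-subjects factor. The Group × Time "interaction will be the primary effect of interest to determine efficacy". No baseline covariate is named.

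Section 2.4.4 confirms that there are only two assessments: a blinded researcher "will collect all data at baseline and after the intervention". Section 2.4.5 makes the COPM the primary outcome, so a baseline COPM score is part of the planned data.

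Baseline differences are addressed in one sentence of Section 2.4.7: "To ensure baseline balance, demographic characteristics and initial assessments will be compared between groups", using t-tests, Mann–Whitney tests or chi-square tests. The section attaches no consequence to the result.

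Section 2.4.6 sizes the trial "assuming an effect size of 0.7 for the COMP tool", with alpha 0.05, power 0.80 and 1:1 allocation, giving 52 evaluable participants and 58 after 10% dropout. It does not say whether 0.7 is in units of the post-score SD or the change-score SD, and it gives no pre-post correlation.

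**The concern.** The choice of model determines how the baseline score is used. A change score subtracts the whole baseline value, as if each extra point at baseline predicted a full extra point afterwards. ANCOVA estimates that slope from the data. When the true slope is below 1, subtraction over-corrects, with two results:

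- **Precision.** The change score carries more noise than necessary. In a trial with 26 evaluable participants per arm, that can be a material loss of power. The same section declines subgroup and exploratory analyses in order to protect power.
- **Chance imbalance.** If one arm starts higher, regression to the mean pulls its change score down, and the treatment estimate moves with it. A significance test at baseline neither prevents nor corrects this. Under randomisation it only asks whether a difference known to be due to chance is large. With small arms, an imbalance big enough to matter can pass the test. One that fails it leaves the reader with no pre-specified adjusted result.

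**Working it through.** **Inputs.** From the document: two arms, one pre and one post score, d = 0.7, alpha 0.05, 26 evaluable per arm (52 in total), two-sided 95% confidence intervals. Assumed, because the document does not give them: pre-post correlation r of 0.3 to 0.9, and equal pre and post SDs unless stated.

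**Step 1: the plan's own figure.** A two-sample t-test with d = 0.7, alpha 0.05 one-sided and power 0.80 needs 26 per arm, or 52 (power 0.801). Then 52 / 0.90 = 57.8, rounded up to 58. Both figures reproduce. A two-sided test needs 34 per arm, or 68. The stated 52 therefore corresponds to a one-sided two-group t-test without a baseline covariate. The mismatch in sidedness is a separate issue. The comparison below is two-sided, to match the planned intervals.

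**Step 2: equivalence.** On simulated data with 26 per arm, the Group × Time F was 11.0899 and the squared t on change scores was 11.0899. They are the same test.

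**Step 3: precision.** With common SD s, the per-participant variances are:

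- change score: 2s²(1 − r)
- ANCOVA: s²(1 − r²)
- ratio, ANCOVA to change score: (1 + r)/2

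**Step 4: power, with d = 0.7 on the post-score SD.** The effective d is 0.7/√[2(1 − r)] for the change score and 0.7/√(1 − r²) for ANCOVA. At r = 0.5 these are 0.7/1 = 0.70 and 0.7/0.866 = 0.81. Power is from the noncentral t, with one further degree of freedom deducted for ANCOVA.

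| r (assumed) | Variance ratio | Power, planned test | Power, ANCOVA | Total N for 80%, planned / ANCOVA |
|---|---|---|---|---|
| 0.3 | 0.65 | 55.3% | 73.7% | 92 / 62 |
| 0.5 | 0.75 | 69.7% | 81.5% | 68 / 52 |
| 0.7 | 0.85 | 89.2% | 93.4% | 42 / 36 |
| 0.9 | 0.95 | >99.9% | >99.9% | 16 / 16 |

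Simulation (20,000 trials per setting) gave 54.9% against 72.8%, 69.7% against 80.6%, and 88.9% against 92.9% at r = 0.3, 0.5 and 0.7. Type I error was 4.7% to 5.1% for both methods.

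**Step 5: the other scale.** If 0.7 is in change-score SD units, the planned test has 69.7% power at every r. ANCOVA has 86.6%, 81.5%, 76.5% and 71.9% at r = 0.3, 0.5, 0.7 and 0.9.

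**Step 6: unequal SDs.** Let k be the post SD divided by the baseline SD, with the baseline SD set to 1. The change-score variance is 1 + k² − 2rk and the ANCOVA variance is k²(1 − r²). The difference is (1 − rk)², which is zero when rk = 1. At k = 1.25:

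- r = 0.5: 1.3125 / 1.1719 = 1.12 (against 1.33 with equal SDs)
- r = 0.7: 0.8125 / 0.7969 = 1.02 (against 1.18 with equal SDs)

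**Step 7: chance imbalance.** Given a baseline difference D between the arms, the change-score estimate shifts by −(1 − r)D with equal SDs.

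- The standard error of a baseline mean difference is √(2/26) = 0.277 SD. At r = 0.5 an imbalance of that size shifts the estimate by 0.5 × 0.277 = 0.139 SD in absolute size, and 0.139/0.7 is about 20% of the assumed effect.
- An imbalance just short of p = 0.05 is about 2.009 × 0.277 = 0.56 SD. It would pass the baseline test, yet shift the estimate by about 0.28 SD, or 40% of the assumed effect.

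**The case against.** The strongest defence is that nothing planned here is invalid. The change-score comparison is unbiased over randomisations and holds its type I error. The shift in Step 7 exists only conditional on an imbalance that has occurred. The model, its factors and the primary effect are clearly named, in a self-described pilot. All of this stands, and it is why the point is a recommended improvement rather than a correction of an error. Nor is baseline ignored: it is subtracted, with a fixed slope.

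A reader might infer more than the document supports in four ways:

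- **That ANCOVA wins whenever r is below 1.** Step 6 shows that this needs a condition on the SDs, and none are given. Section 2.4.2 has participants choose activities they find difficult, which could compress baseline scores and make the post SD the larger one.
- **That the trial is underpowered and ANCOVA restores it.** Section 2.4.6 does not state the scale of 0.7. On the post-score SD at r = 0.7, the planned test already has 89% power. At r = 0.3 on that scale ANCOVA reaches only 74%, and on the change scale at r = 0.9 only 72%. ANCOVA is therefore no sure remedy for the one-sided sample size.
- **That the planned ANOVA is at fault for losing participants without a post score.** ANCOVA on the post score loses the same participants. Missing-data rules are commonly left to a fuller document.
- **That the change is costless.** It uses one degree of freedom and assumes a roughly linear baseline relation.

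None of these points favours the planned model over the adjusted one. They limit the size of the claim.

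**Conclusion.** The point holds as a should-fix matter of efficiency and conditional accuracy. The equivalence to a change-score t-test is exact and needs no assumption. The size of the loss does: with equal SDs and d = 0.7 on the post-score SD, ANCOVA adds about 18, 12 and 4 percentage points of power at r = 0.3, 0.5 and 0.7. The gain is nearly nil at about 0.9, and smaller throughout if the post SD exceeds the baseline SD. The vulnerability to chance imbalance is about 20% of the assumed effect for a one-standard-error imbalance at r = 0.5. The wording that baseline testing will ensure balance is wrong whatever r is: such tests cannot ensure balance, and they do not adjust the estimate.

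**What to change.** In Section 2.4.7:

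- Replace the primary analysis with a linear model of post-intervention COPM on allocated group, with baseline COPM as covariate. Report the adjusted mean difference with its two-sided 95% confidence interval.
- Use the same model for each secondary outcome, with that outcome's own baseline value as covariate.
- Remove the baseline significance tests and the statement that they ensure balance. Present baseline characteristics and scores descriptively by arm, and align the baseline table announced in Section 3.

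The cost is a wording change, one degree of freedom and the linearity assumption. No extra patients or data are needed, since both scores are already planned, and SPSS fits the model. The change should be made before outcome data are seen, so that the choice between adjusted and unadjusted results cannot depend on them. The sidedness of the sample size calculation still needs its own correction.

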
#### 2.4.3. Control Group

Participants included in the control group will continue with their usual treatment and will receive a pamphlet containing information on fatigue management. The selection of usual care as a comparator will be based on the pragmatic nature of the research question, which seeks to evaluate the effectiveness of the intervention against existing clinical practices. By utilizing this design, we aim to measure the incremental benefit of the intervention relative to the outcomes of patients receiving individualized care in a real-world clinical environment [21].

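### The primary two-time-point mixed ANOVA is a change-score test on complete pairs; a baseline-adjusted or common-baseline model would be more precise and would not be biased by baseline-related loss

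*Protocol article*

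**What the plan says.** - **Method (2.4.7):** the primary analysis "will be conducted using a two-way mixed-design ANOVA". Time has two levels ("Pre- vs. Post-intervention) as the within-subjects factor"), and the Group × Time "interaction will be the primary effect of interest to determine efficacy".
- **Data (2.4.4, 2.4.5):** an assessor blinded to allocation "will collect all data at baseline and after the intervention", so there is one score before and one after. "The primary outcome in this study will be the Canadian Occupational Performance Measure (COPM").
- **Dropout (2.4.6):** 52 participants are needed. "Assuming a 10% dropout rate, a total of 58 participants should be included in this study", 29 per arm.
- **Aim (2.4.3):** usual care is chosen as comparator because of the "pragmatic nature of the research question, which seeks to evaluate the effectiveness of the intervention against existing clinical practices".
- **Software (2.4.7):** "Data analysis will be performed using the Statistical Package for the Social Sciences version 24".

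The article gives no analysis population and no missing-data method. Both are commonly left to a fuller document that is not shown, so their absence is not the point here. The point is the method that the article does name.

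**The concern.** A repeated-measures ANOVA with two time points needs both scores from each participant. Someone with only a baseline COPM adds nothing to the Group × Time test unless a post score is imputed first. The test also works on raw change. Change is normally correlated with the baseline value, so if the people lost from one arm have unusually high or low baselines, the mean change of those who remain shifts for reasons unrelated to treatment.

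Unequal loss is possible in this design: one arm attends 16 sessions (8 weeks × 2, section 2.4.2) and the other continues usual care with a pamphlet. At stake are the size of the primary estimate, the error rate of its test, and precision that baseline data already being collected could supply at no cost to participants.

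**Working it through.** **1. The plan's own figures.** 52/0.9 = 57.8, rounded up to 58, so 58 reproduces. Budgeted loss is 58 − 52 = 6 (10% of 58 = 5.8), or 3 per arm if equal. The 52 is taken as given here. At an effect of 0.7 it reproduces with a one-sided t-test (25.94, so 26 per arm) but not with a two-sided one (34 per arm, 68 in all); that is a separate matter.

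**2. What the named test is.** With two time points,

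F(Group × Time) = [(mean change, TOT − mean change, control) / (s_change × √(1/n1 + 1/n0))]² = t².

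On 58 simulated participants with 6 post scores missing, both routes gave 11.98 on 50 residual degrees of freedom, from 52 complete pairs.

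**3. Precision.** Let pre and post scores have SD 1 and correlation ρ. The article does not give ρ.

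- Variance of change: 2(1 − ρ).
- Variance of the post score given baseline: 1 − ρ².
- Ratio of standard errors, adjusted to change-score: √[(1 + ρ)/2].

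| ρ (assumed) | SE ratio | Reduction |
|---|---|---|
| 0.3 | √0.65 = 0.81 | 19% |
| 0.5 | √0.75 = 0.87 | 13% |
| 0.7 | √0.85 = 0.92 | 8% |

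In simulation at ρ = 0.5 with 26 per arm, after the cost of estimating the slope, the mean standard error falls from 0.276 to 0.242, about 12%.

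**4. Bias.** Simulation settings: 29 per arm, ρ = 0.5 (so the SD of change is also 1), true effect 0.70, 40,000 runs per case. Leaving is driven by the named quantity plus noise of equal variance. None of these settings comes from the article. The adjusted column is a baseline-adjusted comparison of post scores on complete pairs.

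| Who leaves | Leavers (TOT / control) | Change-score test | Baseline-adjusted |
|---|---|---|---|
| Unrelated to scores | 3 / 3 | 0.70 | 0.70 |
| High baseline | 3 / 3 | 0.70 | 0.70 |
| High baseline | 3 / 0 | 0.77 | 0.70 |
| High baseline | 6 / 0 | 0.82 | 0.70 |
| Low baseline | 3 / 0 | 0.63 | 0.70 |
| Low baseline | 6 / 0 | 0.58 | 0.70 |
| Poor response | 3 / 3 | 0.70 | 0.70 |
| Poor response | 3 / 0 | 0.84 | 0.81 |
| Poor response | 6 / 0 | 0.95 | 0.89 |

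With no true effect, the change-score test at a nominal 5% rejects as follows:

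- Baseline-related loss in TOT only: about 5.9% (3 leavers) and 7.3% (6), against about 5% after adjustment.
- Response-related loss in TOT only: about 8.5% and 15.6%, against 7.7% and 12.9% after adjustment.
- Response-related loss of 3 in each arm: about 6.2%.

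**5. A simple bound for the sensitivity analysis.** If completers gain 0.70 and k TOT leavers end with the control-arm change, the all-randomised effect is 0.70 × (29 − k)/29. This is 0.70 × 26/29 = 0.63 for k = 3 and 0.70 × 23/29 = 0.56 for k = 6.

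**The case against.** A reader might infer that the plan deletes its dropouts and so answers a completers' question in a trial that calls itself pragmatic. The documents do not support that, for four reasons.

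- Section 2.4.7 names a test, not an analysis population. A mixed ANOVA can be run on imputed data.
- Section 2.4.4 does not tie the post assessment to attendance. Someone who stops training but is assessed is already in the comparison, in the allocated arm.
- Raising 52 to 58 is ordinary protection of power under any analysis.
- In section 2.4.3 the pragmatic wording justifies the choice of comparator and commits to no analysis set.

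It can also be said that the largest biases come from placing all the loss in one arm. Six TOT leavers and no control leavers means 6/29 = 21% loss against 0%, whereas the plan inflates both arms equally. At the planned 3 per arm, even response-related loss gives 0.70. Finally, changing the model does little when loss depends on unobserved response: 0.84 falls only to 0.81, and 0.95 to 0.89.

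All of this stands, and it limits the claim. It does not touch the algebra in step 2, the gain in precision in step 3, or the removal of bias when one-arm loss is related to baseline.

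**Conclusion.** The point holds as a choice of a weaker method, not as a declared exclusion of dropouts. The named test is a change-score t-test on complete pairs. Compared with a baseline-adjusted or common-baseline model it gives up about 12% in standard error at an assumed correlation of 0.5 (8% to 19% for correlations of 0.7 to 0.3). It is biased in either direction if loss in one arm is related to baseline COPM: 0.77 to 0.82 or 0.63 to 0.58 against a true 0.70 in the cases above. Adjustment removes that bias, provided the baseline relation is roughly linear.

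It would go too far to say that the primary test's error rate is not 5%, or that the effect will be inflated. Bias from response-related loss needs that loss to differ by arm. The 0.84 to 0.95 range is an upper case, the documents give no evidence for it, and the better model does not remove it. The change is worth making because it is cheap and dominates the stated method on data already collected.

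**What to change.** 1. Replace the mixed ANOVA as primary analysis with a likelihood-based model of pre and post COPM that has a common baseline mean, so that the group effect enters only at the post visit. A comparison of post COPM adjusted for baseline gives essentially the same answer. The common-baseline model also uses the baseline scores of people without a post score. SPSS MIXED can fit it.
2. State that participants are analysed in their allocated arm, and that the post assessment already scheduled is sought from every randomised participant, whether or not they still attend sessions. This is the only step that reduces missing outcomes themselves.
3. Pre-specify one sensitivity analysis by multiple imputation in which TOT dropouts are given control-like change. Do not fill in a single mean, which understates variance. Report it as a sensitivity analysis, not as a condition for claiming effectiveness. It tests one defined departure and does not cure every form of response-related loss.

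**Cost:** a few lines of analysis text, a little more analysis work, and follow-up of a handful of participants. The estimate may come out slightly less favourable to training.
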